### Recruitment {15}

The recruitment is the same as described in the protocol for our related trial [IMI2-PainCare-BioPain-RCT3] see [2] for more details.

## Assignment of interventions: allocation

### Sequence generation {16a}

Randomization is done blind to investigators as described previously [2] and will be by site.

Subjects will be enrolled by the participating sites and assigned to intervention sequence according to enrolment number per study site.

The randomization list (per site) will be built in blocks of four “4-period sequences,” these sequences being random permutations of the four 4-period sequences of a (basic) Latin square. Each block (allowing the sequential allocation of four subjects) will use an own (new) random permutation of the Latin squares’ four rows.

At the first study period day, before first IMP administration, subjects will be randomized to receive the lowest available randomization number at the site.

### Concealment mechanism {16b}

Each IMP will be administered overencapsulated as single oral dose (two capsules).

A sealed decoding envelope per treatment period will be provided for each randomization number. Each envelope will contain the identification of the IMP allocated to that subject.

### Implementation {16c}

The implementation is the same as described in the protocal for our related rial [IMI2-PainCare-BioPain-RCT3] see [2] for more details. Briefly, the IMPs will be purchased centrally by the Heidelberg University Hospital Pharmacy, which will perform the manufacturing of placebo capsules, the overencapsulation, the packaging, and the labeling of the IMPs, in compliance with applicable local regulations. Detailed information about the packaging and labeling is laid down in a specification document (available on request). The Heidelberg University Hospital Pharmacy will also provide the allocation sequence and sealed envelopes.

Storage conditions will be specified on the labels of the IMPs according to applicable EU and local regulation. The IMPs will be stored in a secure place with restricted access and temperature monitoring. The IMP delivery (shipping), return, and disposal will be performed in accordance with the specification document (available on request). All sites will be licensed according to local law for the receipt, storage, handling and administration of narcotics.

General unblinding (by the statisticians) will only take place after the trial has been completed and the database is locked, except for single-subject unblinding in emergency situations.

## Assignment of interventions: blinding

### Who will be blinded {17a}

As described for RCT3 [2], the investigator/trial personnel and subjects will be blinded to the assignment of pregabalin, tapentadol, lacosamide, and placebo (double-blind procedure).

The personnel analyzing the plasma samples for PK analysis will be unblinded during the bioanalytical analysis but will supply their data to the trial database in a blinded fashion.

### Procedure for unblinding if needed {17b}

Each envelope contains the identification of the IMP allocated to that subject. The investigator may only break the code (open the envelope) when it is necessary and in the subject’s interest to identify the given IMP. If a sealed decoding envelope needs to be opened in an emergency case, the reason and time for unblinding as well as the staff member performing or informed of the unblinding is documented.

If required by local regulations, the IEC needs to be informed.

## Data collection and management

### Plans for assessment and collection of outcomes {18a}

#### Collection of pharmacokinetic data

The collection of pharmacokinetic data is the same as described in the protocol for our related trial [IMI2-PainCare-BioPain-RCT3] see [2] for more details.

#### Collection of demographic data and other baseline characteristics

As detailed for RCT3 [2], investigators will collect demographic data, concomitant medication, and medical history and will check for abstinence of alcohol consumption.

At the screening visit, investigators will perform a focused neurological examination in the presence of any clinically evident sensory disorder, a 12-lead electrocardiogram (ECG) to specifically check for signs of 2nd or 3rd degree atrioventricular (AV) block, a urine test to check for pregnancy and drug abuse and a blood sample will be collected to verify normal renal and hepatic functions.

#### Collection of pharmacodynamic data

All participating centers have the equipment and expertise required for acquisition of the pharmacodynamic data. Each sponsor will provide a detailed operational manual for the collection of PD data.

#### RIII recording

Electrical stimulation of the sural nerve evokes a flexion reflex in the lower limb consisting of an early, inconstantly present component, called the RII reflex and a late, stable, response, the RIII reflex. RIII reflex is a pure nociceptive reflex, mediated by A-delta fibers, and corresponding to the (subclinical) withdrawal of the stimulated limb.

The RIII reflex will be evoked after sural nerve stimulation at the lateral malleolus using a train of five square electrical pulses delivered at a stimulus frequency of 200 Hz, randomly applied every 15–20 s (to avoid habituation). The stimulus intensity used to evoke the reflex will correspond to 1.5× the threshold of the RIII component. The RIII threshold will be defined as the stimulation intensity generating stable reflex responses at a rate of ≥60% after a series of 20 stimuli [3].

The RIII reflex will be recorded in the sitting position, and subjects will be relaxed with their lower limbs positioned to achieve complete muscle relaxation, with the knee flexed at 130° and the ankle around 90°. The RIII reflex will be recorded with standard surface electrodes placed over the short head of the biceps femoris, after carefully cleaning the skin. The recording electrode will be positioned proximally, on the belly of the short head of the biceps femoris muscle, and the reference electrode will be placed on the biceps tendon. Twelve responses will be recorded. Verbal NRS ratings of pain intensity will be collected after each stimulus and after the entire block (0 = no pain at all, 100= most intense imaginable pain).

The RIII onset latency varies between 85 and 130 ms. Responses with latencies between 40 and 60 ms should be classified as the early non-nociceptive RII response. The RIII amplitude will be measured as the area under the biceps femoris muscle EMG curve, between 80 and 130 ms. The area under the EMG curve must be measured for each trial.

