**Primary endpoints:**	
1. To test if the percentage of change of the RIII area of the flexion reflex at the time point t60 post-drug administration vs the pre-drug time point, differs in the tapentadol period as compared to the placebo period, at the sensitized lower limb.	
2. To test if the percentage of change of the N13-SEP amplitude at the time point t60 post-drug administration vs the pre-drug time point, differs in the tapentadol period as compared to the placebo period, at the sensitized upper arm.	

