#### Definition of other pre-specified analyses

The following secondary endpoints will be investigated and compared across the four treatment groups:The percentage of change in the RIII threshold across all post-drug time points vs. the pre-drug baseline time point, at the sensitized limbThe percentage of change in the intensity of the sensation elicited by the electrical stimulation for the RIII reflex recording, as assessed with the NRS 0-100 points, at time point T+60 min post-drug administration vs. the pre-drug time point, at the sensitized limb.The percentage of change of the RIII area of the flexion reflex at the time point t60 post-drug administration vs the pre-drug time point, at the non-sensitized limb.

Additional exploratory endpoints will be:The percentage of change of the R2 recovery cycle at 250 and 750 ms interstimulus time interval.The N13-SEP and R2 latency changes.RIII flexion reflex changes at the sensitized and non-sensitized side (area, threshold, perception) across the four PD time points in the four study periods.Somatosensory evoked potential variables changes (amplitude and latency of N9, N13, and N20) across the four PD time points in the four study periods.Changes in amplitude ratios of somatosensory evoked potentials (N13/N9, N13/N20, N20/N9) across the four PD time points in the four study periodsR2 recovery cycle at the different interstimulus time intervals, across the four PD time points in the four study periodsGender differences of neurophysiological and hyperalgesia variablesCorrelation between subject’s level of anxiety and expectation of pain and PD1 neurophysiological variablesCorrelation between subject’s expectation of pain relief and hyperalgesia variablesPK/PD analysis. As both drug concentrations and biomarker responses are measured at several time points post-drug administration, the relationship between drug levels and select biomarkers will be explored and modelled.

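### The RIII area window closes at 130 ms, the latest onset the protocol itself gives, so primary endpoint 1 cuts late responses and cannot separate a latency change from a change in reflex size

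*Protocol article*

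**What the plan says.** In the protocol article, *RIII recording* gives two time ranges in the same paragraph. The first is where the reflex begins: "The RIII onset latency varies between 85 and 130 ms". The second is where it is measured: "The RIII amplitude will be measured as the area under the biceps femoris muscle EMG curve, between 80 and 130 ms". The earlier, non-nociceptive component is placed well before the window: "Responses with latencies between 40 and 60 ms should be classified as the early non-nociceptive RII response". The window applies to every sweep: "The area under the EMG curve must be measured for each trial". The section gives no window tied to onset, no rule for late responses and no response duration.

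This area is the first primary endpoint (Table 4): "To test if the percentage of change of the RIII area of the flexion reflex at the time point t60 post-drug administration", compared with the pre-drug value, tapentadol against placebo. It also serves the first key secondary analysis (pregabalin and lacosamide) and a secondary endpoint at the non-sensitized limb.

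*Definition of other pre-specified analyses* includes "The N13-SEP and R2 latency changes" and the latencies of the other SEP components. For RIII it names area, threshold and perception only.

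**The concern.** An onset is the moment a response starts. A window that ends at the latest accepted onset contains none of a response starting then, and only the first part of any response starting shortly before. The measured area then depends on two things, how large the reflex is and how early it starts, although the endpoint is meant to reflect the first.

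Two consequences follow for primary endpoint 1. First, it is a percentage change, so a subject whose response is mostly outside the window has a small pre-dose denominator, and small shifts in onset between sessions produce large percentage swings. Second, if any treatment altered RIII latency, the endpoint would record it as a change in size, and no listed RIII variable would reveal it.

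**Working it through.** **Inputs from *RIII recording*.** Onset L between 85 and 130 ms; window 80 to 130 ms, 50 ms wide; RII latency 40 to 60 ms; stimulus "a train of five square electrical pulses delivered at a stimulus frequency of 200 Hz". **Assumed, because not given:** burst duration D (20 to 60 ms), burst shape, onset distribution, and any delay. The plan states no figure to reproduce here.

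**Time inside the window** = 130 - L, and a burst is held whole only if L + D is at most 130. **Effect of a 5 ms delay with reflex size unchanged**, for a rectangular burst already cut by the window (D at least 130 - L) = -5/(130 - L).

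| Onset L (ms) | Time in window (ms) | Change from 5 ms delay, burst already cut |
|---|---|---|
| 85 | 45 | -5/45 = -11% |
| 100 | 30 | -5/30 = -17% |
| 110 | 20 | -5/20 = -25% |
| 120 | 10 | -5/10 = -50% |
| 130 | 0 | not defined |

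**Where the change is zero.** If the burst ends at least 5 ms before 130 ms (L + D + 5 at most 130), a 5 ms delay costs nothing. Onset 85 ms with D of 20 to 40 ms ends at 105 to 125 ms, giving 0%. Onset 100 ms with D = 25 ms ends at 125 ms, also 0%.

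**Dependence on shape.** With a half-sine burst, a 5 ms delay at onset 100 ms gives -19% for D = 40 ms but -7% for D = 30 ms, against -17% for a rectangular burst in both cases.

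**How many responses are cut.** If onsets were uniform over the 45 ms from 85 to 130 ms, the share cut would be D/45: 20/45 = 44%, 30/45 = 67%, and all of them at D of 45 ms or more.

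**Denominator.** At onset 120 ms the window holds 10 ms. A session-level shift of 5 ms later or earlier leaves 5 or 15 ms (the latter if D is at least 15 ms), a swing of -50% or +50% with no change in size. At onset 85 ms with D = 40 ms the same shifts give 0%.

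**Stable truncation.** If a constant share f of the response is captured, (fA1 - fA0)/(fA0) = (A1 - A0)/A0, so f cancels. It cancels only largely, not fully, once background EMG B is in the area: f(A1 - A0)/(fA0 + B), which shrinks as f falls.

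**Time zero.** Five pulses at 200 Hz span 4 x 5 = 20 ms, and neither range says which pulse it counts from. If onset were counted from the first pulse and the window from the last, the window would be 100 to 150 ms on the onset scale: 20 ms would be gained at onset 130 ms, but the first 15 ms of a response at 85 ms would be lost. The reverse would close the window at 110 ms. Nothing in the text says the origins differ.

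**The case against.** The strongest reply is that the same window is used before dosing, after dosing and under placebo in a within-subject crossover. A stable loss therefore largely cancels, and no statement in the protocol says that tapentadol, pregabalin or lacosamide delays RIII. This stands. A reader might infer that the endpoint will score a drug-related delay as RIII depression, but the documents do not show that such a delay occurs.

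A reader might also set the percentages above against the 20% depression used in *Sample size*. The comparison does not hold. The percentages apply to a single response at a chosen onset and burst length, while 20% is a group effect; matching it would need mostly mid-to-late onsets and a systematic drug-related delay. The same section also plans on a 53.7% change. How many subjects have late onsets is unknown.

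The word onset may itself be a slip for the span of the response. If so, the wording needs correction rather than the window. The text does not settle this, so the two ranges must be reconciled either way.

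Finally, *Methods for additional analyses* foresees variants of primary endpoint parameter extraction, and *Collection of pharmacodynamic data* promises an operational manual. These may add detail, but the variants are exploratory, and neither provision changes the window stated for the primary endpoint.

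**Conclusion.** The point holds as an internal inconsistency in the definition of primary endpoint 1. On the protocol's own figures, and taking onset at its word with a common time zero, a response it accepts as RIII has 10 ms in the window at onset 120 ms and none at 130 ms. That part needs no assumption about burst length.

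It follows that the endpoint cuts late-onset responses, makes the percentage change unstable in those subjects, and cannot distinguish a latency change from a size change. Early, short bursts are measured in full. The size of the effect on the trial cannot be fixed from the document, because burst length, burst shape and the distribution of onsets are absent. The -17% and -25% figures illustrate sensitivity under stated assumptions and are not an estimate of bias. Bias in the tapentadol contrast is possible, not shown.

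**What to change.** Reconcile the onset range with the window, and state the time zero for both. Keep the 80 ms start, which already excludes the 40 to 60 ms RII. End the window after the latest stated onset plus the response duration, 130 + D: 150 ms for D = 20, 170 ms for D = 40, 190 ms for D = 60 (D assumed). A delay that stays within the stated onset range would then leave the area unchanged.

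Set one fixed end point for all subjects and sessions from pooled pre-dose recordings, blind to treatment, before the SAP is finalized and the database locked. Keep 80-130 ms as a sensitivity analysis and add RIII onset latency to the reported RIII variables. A window anchored to each subject's pre-dose onset and only as long as the burst would not cure the problem: with a 50 ms burst and a 50 ms anchored window, a 5 ms delay still removes 5/50 = 10%.

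The cost is a change of wording and re-extraction, which *Data management* already places at one center. It assumes that the stored sweeps run to the new end point; sweep length is not given. The longer window also admits more background EMG. Its width becomes 70, 90 or 110 ms instead of 50 ms, or 1.4, 1.8 or 2.2 times the present interval. Subtracting pre-stimulus baseline EMG can offset this, if that baseline was recorded.

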#### N13 recording

The N13 spinal evoked potential will be elicited by electrical stimulation of the ulnar nerve at the wrist. The cathode will be placed 2 cm proximal to the wrist crease, the anode on the wrist crease. The ulnar nerve will be stimulated using electrical pulses of 0.1 ms of duration, with a frequency of 4 Hz. The intensity will be set at the threshold for evoking muscle twitch in the ulnar nerve muscles of the hand. The N13 will be recorded with posterior spinal cervical electrode placed over the 6th cervical spinous process (Cv6). The reference will be on the anterior neck at the level of the glottis on the midline (AC). The ground electrode will be placed on the stimulated limb between the stimulation site and the recording electrode. Muscle artifacts will be eliminated by making the subject as comfortable as possible. The subject will lie on a medical cot in a complete relaxed position. Two blocks of 650 trials will be collected, superimposed, in order to evaluate the reproducibility, and averaged. The N13 amplitude will be measured from the positive peak of the P9 to the negative peak of the N13 (when the P9 is not clearly identified, the amplitude will be measured from the isoelectric line).

#### Additional SEP components

N9 is a near-field potential generated by afferent action potentials in the brachial plexus. Electrodes will be placed bilaterally, over the Erb’s point, within the angle formed by the posterior border of the clavicular head of the sternocleidomastoid muscle and the clavicle, 2–3 cm above the clavicle. The recording electrode ipsilateral (EPi) to the site of stimulation and the reference electrode contralaterally (EPc). The N9 is the principal negative peak seen in the Epi-EPc channel. The amplitude of N9 will be measured on the Epi-EPc channel from its peak to that of the initial positive deflections.

N20-P25 is generated in the primary somatosensory cortex, in the posterior bank of the central sulcus. The locations of scalp electrodes will be specified using the 10–20 International system of EEG electrode placement. Parietal scalp electrodes will be positioned 5 cm posterior to Cz and 7 cm lateral to midline, contralateral to the site of stimulation (Pc). Reference electrode will be placed on Fz. N20 represents the largest early negative deflection at Pc. The N20 peak is usually identified as a portion of the negative potential just preceding the sharp drop-off toward the succeeding cortical positive peak P25. The P25 component will be recognized as the main prominent positive peak succeeding the N18-N20 complex at Pc. The amplitude of the cortical potentials will be measured from the N20 peak to the P25 on the Pc-Fz channel.

#### R2-blink reflex recording

The blink reflex is a brainstem reflex, mediated by large myelinated non-nociceptive fibers, consisting of an early component, the R1, and a late component, the R2, mediated by a polysynaptic circuit lying in the brainstem reticular formation.

The blink reflex will be elicited by electrical stimulation of the supraorbital nerve. To record blink reflex, the subject will lie on a medical cot in a relaxed position, with the gaze down. The supraorbital nerve will be stimulated immediately above the supraorbital notch. The EMG signals will be collected from the orbicularis oculi muscle bilaterally. The recording electrode will be placed over the muscle, the reference electrode at the lateral angle of the eye. Five responses will be recorded. The R2 amplitude will be measured as the area under the muscle EMG curve between 25 and 85 ms. The recovery cycle of the R2 will be investigated with paired stimulation of the supraorbital nerve (using the same stimuli parameters applied for the blink reflex recording). Interstimulus time intervals of 250, 500, and 750 ms will be used. For each interstimulus time interval, seven trials will be collected.

The recovery cycle will be then calculated by expressing the area of the response to the second shock (test) as a percentage of the area of the response to the first shock (conditioning).

#### Non-neurophysiologically derived pharmacodynamic data

The non-neurophysiologically-derived pharmacodynamic data are the same as described in the protocol for our related trial [IMI2-PainCare-BioPain-RCT3] see [2] for more details. Briefly the following data will be collected:

##### Pain intensity and unpleasantness ratings

The subjects will be also asked to rate the average unpleasantness/pain of each PD block using a 101-point unpleasantness/pain rating scale where 0 is defined as “not unpleasant/painful at all” and 100 is defined as “extremely unpleasant/painful.”

##### Patient-reported outcome measures (PROMs)

During the screening visit, subjects will be asked to complete a set of PROMs assessing their psychological traits. During each study period, subjects will be asked to complete an additional set of PROMs assessing their expectations, tiredness, and anxiety. The PROMs will be collected via questionnaires in the local language. Scores calculated from these questionnaires will be entered in the source paper documentation before entering into the electronic CRF. The subjects will be instructed on how to fill out the questionnaires.

The following PROMs will be completed during the screening visit, in the following order: (1) *Self-assessment of general health using the PROMIS Global-10 questionnaire*, a global health assessment tool that allows measurements of symptoms, functioning, and healthcare-related quality of life for a wide variety of chronic diseases and conditions; (2) *Self-assessment of self-efficacy using 3 items of the General Self Efficacy Scale (GSE)* [29], a psychometric scale that is designed to assess optimistic self-beliefs to cope with a variety of difficult demands in life; (3) *Self-assessment of trait anxiety using the General Anxiety Disorder-7 questionnaire (GAD-7)*, a brief scale on anxiety; (4) *Self-assessment of depression using the Patient Health Questionnaire-9 (PHQ-9)*, a diagnostic tool for mental health disorders, specific to depression; (5) *Self-assessment of pain catastrophizing using the Pain Catastrophizing Scale (PCS)* [30], a 13-item scale, broken into three subscales being magnification, rumination, and helplessness; (6) *Self-assessment of pain sensitivity using the Pain Sensitivity Questionnaire (PSQ)* [31].

The following PROMs assessing subject expectations will be completed at the beginning of each study period: (1) *Anxiety* will be assessed by asking subjects: “On a scale of 0–100, please rate, how anxious you are about the upcoming experiment, with 0 being ‘not anxious at all’ and 100 being ‘extremely anxious’”; (2) *Pain expectation* will be assessed by asking subjects: “On a scale of 0-100, please rate how much pain do you anticipate experiencing during the upcoming experiment, with 0 being ‘no pain at all’ and 100 being ‘pain as bad as you can imagine’”; (3) *Expectation of IMP-induced pain relief* will be assessed by asking subjects: “On a scale from 0 to 100, please rate how much pain relief you expect from the medication, with 0 being ‘expecting no relief’ and 100 being ‘expecting complete relief’.”

The PROMs assessing tiredness and anxiety will be assessed 5 h after IMP administration: (1) *Self-assessment of tiredness*. The subject will be asked: “On a scale of 0–100, please rate, how alert or sleepy you feel right now, with 0 being ‘very alert’ and 100 being ‘very sleepy’”; (2) *Self-assessment of state anxiety using the State and Trait Anxiety Inventory (STAI-Y)* [32].

